## 4 TRIAL OBJECTIVE AND PURPOSE

### 4.1 PRIMARY OBJECTIVE

To evaluate the safety and efficacy of RMD given in combination with a booster vaccination with MVA.HIVconsv for reduction of the viral reservoir in a cohort of early suppressed HIV-positive individuals who previously received an heterologous vaccination regimen with ChAd/MVA.HIVconsv in the BCN01 trial.

### 4.2 SECONDARY OBJECTIVES

1. To evaluate HIV reactivation capacity and effect of RMD on CTL functionality through an *ex vivo* model and to assess its *in vivo* translation
2. To perform a population PK/PD analysis to assess the association between HIV expression and CTL functionality effect *in vivo* with RMD exposure
3. To evaluate the immunogenicity of booster vaccinations with MVA.HIVconsv before and after RMD administration and the effect on viral rebound control after discontinuation of cART.

## 5 TRIAL DESIGN

### 5.1 TYPE OF TRIAL

Multicenter, open-label, single arm clinical trial.

### 5.2 DESCRIPTION OF THE DESIGN

See attachment A for study diagram.

All 24 early-suppressed HIV positive individuals enrolled in the extension phase of BCN01 trial and who meet all eligibility criteria will be invited to participate.

The trial will be divided in two phases with different primary endpoints. In the first part of the trial (**Part A: intervention phase**) RMD will be administered after a first booster vaccination with MVA.HIVconsv. The primary endpoint will be safety and efficacy of the combined intervention in the reduction of viral reservoir. Secondary endpoints will include the establishment of an *ex vivo* model to assess HIV reactivation and potential CTL functional impairment in the context of RMD and the development of a population PK/PD analysis to relate RMD effects with its exposure (see below endpoints 1 and 2 for details).

In the second part of the trial (**Part B: MVA.HIVconsv plus MAP**) a second booster vaccination with MVA.HIVconsv will be given 4 weeks after last RMD infusion -to cover any potential impairment of previously induced CTL response due to RMD administration. After an interim futility analysis (w13), a MAP will be offered to all participants at week 17. Here, secondary endpoints will include all viral rebound efficacy clinical outcomes as well as the study of correlates of control (see below description of endpoints 3 for details)

## 5.3 ENDPOINTS

### 5.3.1 Primary endpoint(s)

1. Safety and tolerability evaluation as measured by  $\geq 3$  grade adverse events (AE) and serious adverse events (SAE).
2. Reduction of the viral reservoir measured in CD4+ T cells by digital droplet PCR (ddPCR) at baseline and 1 week after 3rd dose of RMD (total HIV-1 DNA copies per  $10^6$  CD4+ T cells)

### 5.3.2 Secondary endpoints

1. To evaluate *ex vivo* capacity of RMD to induce HIV expression in resting CD4+ T cells and to influence CTL functionality. Stored biological samples from the BCN01-RO phase will be used. Culture incubations with RMD will simulate Cmax concentrations of the clinical dose ( $5\text{mg}/\text{m}^2$ ). Results of the *ex vivo* system will be associated with the frequency of detected HIVconsv-specific induced T cells and compared to the observations during the intervention phase to assess its *in vivo* translation. *Ex vivo* measurements will include:
  - 1.1. Cell-associated RNA (CA-RNA)
  - 1.2. Viability, necrosis and apoptosis levels by flow cytometry and using Annexin, 7AAD, CD3, CD4 and CD8 markers
  - 1.3. Activation, exhaustion and proliferation capacity
  - 1.4. IFN $\gamma$  production assessed by ELISPOT and after PBMC stimulation with HIVconsv-specific peptides, as well as other non-related pathogens, such as EBV and CMV.
  - 1.5. Evaluation of the in-vitro viral inhibition capacity in the presence of RMD to a panel of 3 viruses (CCR5 and CxCR4)
2. To perform a population PK/PD analysis to assess the relationship between HIV expression and CTL functionality effect *in vivo* with RMD exposure. Specific endpoints will include:
  - 2.1. RMD plasma concentrations at the end and 0.5, 1, 2, 4, 8, 10 and 20 hours after the 1st RMD infusion. RMD plasma concentrations at the end and 8

- hours after the 2nd and 3rd infusions. Plasma concentrations will be measured by LC-MS/MS, and will be used to develop a population PK model. Parameters will include: volumes of distribution, total and intercompartmental plasmatic clearance, maximum and minimum concentrations and area under the curve.
- 2.2. *In vivo* capacity of RMD to induce HIV expression in resting CD4+ T cells measured by CA-RNA and ultrasensitive plasma viral load (SCA) before RMD infusion and after 24 and 72h (RMD1), 12 and 72h (RMD2) and 12, 72 and 7 days (RMD3)
  - 2.3. *In vivo* levels of Histone H3 acetylation in lymphocytes before RMD infusion and after 24 and 72h (RMD1), 12 and 72h (RMD2) and 12, 72 and 7 days (RMD3)
  - 2.4. *In vivo* IFN $\gamma$  production assessed by ELISPOT and after PBMC stimulation with HIVconsv-specific peptides before RMD infusion and after 24 and 72h (RMD1), 12 and 72h (RMD2) and 12, 72 and 7 days (RMD3)
  - 2.5. *In vivo* CTL toxicity assessment based on the most relevant marker from Endpoint 1 (viability, activation, ex) before RMD infusion and after 24 and 72h (RMD1), 12 and 72h (RMD2) and 12, 72 and 7 days (RMD3)
  - 2.6. Development of a population PK/PD analysis to integrate pharmacokinetics of RMD and *in vivo* observed effects of RMD
3. To evaluate the immunogenicity of booster vaccinations with MVA.HIVconsv before and after RMD administration and the effect on viral rebound control after discontinuation of cART.
    - 3.1. To evaluate immunogenicity of booster vaccinations, HIVconsv-specific T cell responses will be measured before, 1, 4 and 8 weeks after both booster vaccinations (MVA1 and MVA2) by IFN $\gamma$  ELISPOT using peptide pools covering different HIV proteins and HIVcons sequences. Total HIVconsv magnitude as well as HIVconsv focus over the rest of HIV-1 specific responses will be compared over time. These results will enable the futility analyses (see section 5.6)
    - 3.2. Evaluation of the effect MVA.HIVconsv boost vaccinations on viral suppressive capacity of CD8+ T cells in vitro, using a flow cytometric assay 4 weeks after MVA2.
    - 3.3. Determine the proportion of individuals who initiate a MAP following the futility analysis
    - 3.4. Determine the proportion of individuals who maintain sustained pVL <2,000 copies/ml during the first 12weeks after treatment cessation.
    - 3.5. Determine the proportion of individuals in whom cART is reinitiated due to viral rebound (2 consecutive pVL >2,000 copies/ml 3-5 days apart), >50% drop in CD4 cell counts, <450 cells/mm^3 and/or symptomatic acute retroviral syndrome.
    - 3.6. Evaluate the emergence of viral resistance during MAP phase
    - 3.7. Evaluate the viral suppression rates 6 months after treatment resumption.

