## 7.3 SUBJECT WITHDRAWAL CRITERIA

### 7.3.1 Related to MVA.HIVconsrv vaccination

First MVA.HIVconsrv vaccination will only be administered if plasma viral load (pVL) is below the limit of detection in 2 consecutive determinations and CD4 cell count > 500 cells/ml at baseline. After RMD administration, low-level viral load detections (pVL<2,000 copies/ml) will be allowed only if suboptimal cART adherence is not suspected.

Any individual for who is being considered for discontinuation or postponement of vaccinations will be discussed with the trial team.

Participants might be discontinued or postponed -if clinical condition or laboratory abnormality is resolved within a maximum window of 10 days- from further vaccination for any of the following reasons:

- Ineligibility (either arising during the study or retrospective having been overlooked at screening).
- A disease, condition or an adverse event (including clinically significant abnormal laboratory values; see below) that develops, regardless of relationship to the study products, if, in the opinion of the principal investigator or designee, further vaccinations would jeopardize the safety of the patient.
- Hematology
  - Hemoglobin < 10.0 g/dl
  - Absolute Neutrophil Count (ANC)  $\leq 1000 /\text{mm}^3$  ( $\leq 1 \times 10^9 /\text{l}$ )
  - Absolute Lymphocyte Count (ALC)  $\leq 600 /\text{mm}^3$  ( $\leq 1 \times 10^9 /\text{l}$ )
  - Platelets  $\leq 50.000 /\text{mm}^3$ ,  $\geq 550,000 /\text{mm}^3$  ( $\leq 50 /\text{L}$ ,  $\geq 550 /\text{L}$ )
- Biochemistry

- Creatinine > 1.3 x ULN
  - AST > 2.5 x ULN
  - ALT > 2.5 x ULN
- Confirmed HIV-1 or HIV-2 re-infection.
- Pregnancy.
- Significant non-compliance with cART regimen or study requirements.
- Receipt of blood transfusion or blood products during this study.
- Participating in another clinical trial of an IMP.
- A serious adverse event judged to be possibly, probably or definitely related to vaccination.
- An adverse event which requires discontinuation of the study product or results in inability to continue to comply with study procedures.
- Loss to follow up.
- The safety of the volunteer would be jeopardized in the opinion of the investigator or sponsor.
- Investigator discretion.
- Significant protocol deviation.

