### 8.1.15 MAP phase monitoring

Monitoring visits during the MAP phase will be performed at BCN-Checkpoint community center (see flow chart below). A specific MAP Phase Monitoring Form (attachment E) will be used to collect data.

During first 12 weeks post-MAP (from week 18 to week 29):

- Weekly visits will be performed, including:
  - o Clinical visit and adverse events register
  - o Reporting of symptoms suggestive of acute retroviral syndrome (including its severity grade):

|                                                  |                                                 |                                       |
|--------------------------------------------------|-------------------------------------------------|---------------------------------------|
|  Fever of unknown origin |  Headache               |  Pharyngitis  |
|  Lymphadenopathy         |  Transaminase elevation |  Lymphopenia  |
|  Oral candidiasis        |  Myalgia/arthralgia     |  Night sweats |

- |                                           |                                           |                                              |
|-------------------------------------------|-------------------------------------------|----------------------------------------------|
|  Fatigue          |  Nausea, vomiting |  Hepato/splenomegaly |
|  Rash             |  Diarrhea         |  Others              |
|  Trombochytopenia |                                           |                                              |

- 5ml blood extraction for :
  - Qualitative viral load test (Xpert HIV-1 Qual de Cepheid)
- Discussion on treatment resumption: recommendation on cART resumption will be assessed based on clinical visit, willingness of patients to resume treatment and detection of viral load in the qualitative test.
- Schedule of next appointment.
- Visits at 2, 4, 8, and 12 weeks after treatment interruptions (weeks 19, 21, 25 and 29) will also include
  - Biochemistry and hematological parameters, viral load and CD4 count (performed at an external Lab)

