  - Plasma and PBMC storage following scheme detailed in attachment K
  - Discussion on treatment resumption once results from Biochemistry, Hematological parameters and CD4 cell count are available (72h): recommendation on cART resumption will be assessed based on clinical visit, willingness of patients to resume treatment, detection of viral load in the qualitative test and/or drop in CD4 cell counts.

After the first 12 weeks post-MAP (from W30):

- Fortnightly visits will be performed, including:
  - Qualitative viral load test (Xpert HIV-1 Qual de Cepheid)
  - Clinical visit, adverse event register
  - Reporting of symptoms suggestive of acute retroviral syndrome (including its severity grade)
  - Discussion on treatment resumption: recommendation on cART resumption will be assessed based on clinical visit, willingness of patients to resume treatment and detection of viral load in the qualitative test.
- Monthly:
  - Biochemistry and hematological parameters, viral load and CD4 count (performed at an external Lab)
  - Plasma and PBMC storage following scheme detailed in attachment K
  - Discussion on treatment resumption once results from Biochemistry, Hematological parameters and CD4 cell count are available (72h): recommendation on cART resumption will be assessed based on clinical visit, willingness of patients to resume treatment, detection of viral load in the qualitative test and/or drop in CD4 cell counts.

|                                                                                                           | Phase 2 (to be performed at BCN-Checkpoint) |    |    |    |    |    |    |    |    |    |    |    |                                                                |    |    |    |    |    |    |    |    |    |    |    |    |    |    |    |    |    |    |    |    |    |  |  |  |
|-----------------------------------------------------------------------------------------------------------|---------------------------------------------|----|----|----|----|----|----|----|----|----|----|----|----------------------------------------------------------------|----|----|----|----|----|----|----|----|----|----|----|----|----|----|----|----|----|----|----|----|----|--|--|--|

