| Efficacy Endpoint                                                                                         |                                             | x  |    |    |    |    |    |    |    |    |    | x  |                                                                |    |    |    |    |    |    |    |    |    |    |    |    |    |    |    |    |    |    |    |    |    |  |  |  |
| # to be shipped to HGTP for processing in the same day (for virological and immunological studies)        |                                             |    |    |    |    |    |    |    |    |    |    |    |                                                                |    |    |    |    |    |    |    |    |    |    |    |    |    |    |    |    |    |    |    |    |    |  |  |  |
| ~ to be shipped to General Lab : results available at Checkpoint (Report by phone to the patients at 72h) |                                             |    |    |    |    |    |    |    |    |    |    |    |                                                                |    |    |    |    |    |    |    |    |    |    |    |    |    |    |    |    |    |    |    |    |    |  |  |  |

If qualitative pVL test is found positive (indicative of pVL >200 copies/ml), following procedures will be performed:

- Blood extraction including:
  - o Viral load, hematological parameters and CD4 count
  - o Plasma and PBMC storage following scheme detailed in attachment K
  - o pVL-pos+3d visit scheduling

pVL-pos+3d visit will be performed at BCN-Checkpoint and will include:

- Clinical visit, adverse event collection
- Reporting of symptoms suggestive of acute retroviral syndrome (including its severity grade)
- Blood extraction including:
  - o Viral load and CD4 count
  - o Genotype resistance test
  - o Plasma and PBMC storage following scheme detailed in attachment K
- cART resumption visit scheduling (pVL-pos + 7 days) at BCN-Checkpoint

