#### 8.1.16 cART resumption visit (7-10 days after first Qual pVL positive)

pVL-pos+7d visit will be performed at BCN-Checkpoint.

Following procedures will be performed:

- Reporting of symptoms suggestive of acute retroviral syndrome (including its severity grade)
- Discussion on treatment resumption based on following considerations (attachment M):
  - o If viral load is >2,000 copies/mL in visits pVL-pos and pVL-pos+3d, and/or clinical symptoms, laboratory abnormalities or significant drops in CD4 T cell counts (>50% &/or <500) have been detected, patients will be recommended to re-start cART immediately.
  - o If viral load is <2,000 copies/mL in visits pVL-pos and >2,000 copies/mL in visit pVL-pos+3d, and/or clinical symptoms, laboratory abnormalities or

significant drops in CD4 T cell counts (>50% &/or <500) have been detected, patients will be recommended to re-start cART immediately.

- If viral load is > or <2,000 copies/mL in visits pVL-pos and <2,000 copies/mL in visit pVL-pos+3d, and NO clinical symptoms, laboratory abnormalities or significant drops in CD4 T cell counts have been detected cART will not be resumed.
- cART prescription\* at the Pharmacy Unit
- Follow-up explanation and cART+4w visit scheduling (or a follow-up MAP visit at BCN-Checkpoint if cART is not resumed)
- CRF data collection

\*cART regimen will at the discretion of the study physician, according to clinical criteria (no changes on patient's previous cART regimen are envisioned as no emergence of drug resistances is expected)

Overall, time since 1st positive HIV-1 Qualitative detection to cART resumption is aimed to be <10 days to avoid fast viral reservoir replenishment.

[figure not shown]

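### Secondary endpoint 3.5 counts fewer restart triggers than the restart rule in section 8.1.16 uses, so read literally it can only undercount protocol-directed cART restarts

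*Protocol*

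**What the plan says.** Section 5.3.2, item 3.5, sets out to "Determine the proportion of individuals in whom cART is reinitiated due to viral rebound (2 consecutive pVL >2,000 copies/ml 3-5 days apart". After that bracket it adds the CD4 criteria, ">50% drop in CD4 cell counts, <450" cells/mm³, and symptomatic acute retroviral syndrome.

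Section 8.1.16 says when participants are advised to restart. Two values above 2,000 lead to restart, as in 3.5. So does a second pattern: "If viral load is <2,000 copies/mL in visits pVL-pos and >2,000 copies/mL in visit pVL-pos+3d, and/or clinical symptoms". Laboratory abnormalities are also on the list. For CD4 the text is: "significant drops in CD4 T cell counts (>50% &/or <500) have been detected, patients will be recommended to re-start cART immediately". Treatment stays off only if the second value is below 2,000 and there are no symptoms, laboratory abnormalities or significant CD4 drops.

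The sequence starts under section 8.1.15: "If qualitative pVL test is found positive (indicative of pVL >200 copies/ml" copies/ml), a quantitative sample is drawn and another follows three days later. For the first 12 weeks of the pause, "Weekly visits will be performed, including" the qualitative test. From week 30, "Fortnightly visits will be performed, including" the same test.

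**The concern.** Item 3.5 reports restarts that section 8.1.16 generates, but the two lists of reasons differ. An analyst who applies 3.5 as printed would leave out a participant who restarted exactly as the protocol advised, for example after one value below 2,000 and a second above it, or at a CD4 count of 470.

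Two things are at stake. The reported restart proportion could be lower than the true proportion of protocol-directed restarts. The secondary endpoints could also fail to reconcile: a participant with a value below and then above 2,000 who restarts within 12 weeks has not kept viral load below 2,000 (endpoint 3.4), yet would be absent from 3.5.

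**Working it through.** The protocol states no figure to reproduce here, so the check is a comparison of the two rules, then an enumeration.

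**Triggers side by side**

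| Trigger | 5.3.2, item 3.5 | 8.1.16 |
|---|---|---|
| Both values >2,000 | yes | yes |
| First <2,000, second >2,000 | no | yes |
| CD4 drop >50% | yes | yes |
| CD4 <450 | yes | yes (within <500) |
| CD4 450–499 | no | yes |
| Acute retroviral syndrome | yes | yes (within clinical symptoms) |
| Other clinical symptoms | no | yes |
| Laboratory abnormalities | no | yes |

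Every entry in the 3.5 column is also in the 8.1.16 column, and four 8.1.16 entries are absent from 3.5. The 3.5 list is therefore a strict subset.

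**Enumeration**

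Factors: first value above or below 2,000 (2), second value above or below 2,000 (2), CD4 drop >50% (2), CD4 band <450, 450–499 or ≥500 (3), retroviral symptoms (2), laboratory abnormality (2). Total: 2 × 2 × 2 × 3 × 2 × 2 = 96 combinations. This assumes no further viral load between the day-3 sample and restart. It counts all symptoms as retroviral syndrome, which favours 3.5.

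- **No restart under 8.1.16:** second value <2,000, CD4 ≥500, and no drop, symptoms or laboratory abnormality, with the first value on either side of 2,000. That is 2 combinations, leaving 96 − 2 = 94 that lead to restart.
- **Not met by 3.5, reading its CD4 wording as drop OR <450:** 3 viral-load patterns (all except both >2,000) × 2 CD4 bands (450–499, ≥500) × 2 laboratory states, with no drop and no syndrome = 12. Two of these are the no-restart combinations, so 12 − 2 = **10 of 94 restart combinations are missed**.
- **Make-up of the 10:** six have a laboratory abnormality (3 × 2). The other four are <2,000 then >2,000 with CD4 ≥500, and CD4 450–499 with each of the three viral-load patterns.
- **Not met by 3.5, reading the CD4 wording as drop AND <450** (the comma allows it): 3 × (2 × 3 − 1) × 2 = 30, and 30 − 2 = **28 missed**.
- **Met by 3.5 without an 8.1.16 restart:** 0 under either reading.
- **If 3.5 used the 8.1.16 criteria:** 0 mismatches in 96.

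These are counts of patterns, not probabilities.

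**Could a later sample close the viral-load gap?** Sometimes. In the first 12 weeks the next weekly test falls on day 7, which is 7 − 3 = 4 days after the day-3 sample and inside the 3–5 day window. If it led to a quantitative value above 2,000 before restart, 3.5 would be met. This is not assured, because section 8.1.16 lists no viral load at the resumption visit and scheduled testing is fortnightly from week 30.

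**Effect per missed restart:** 1/n. With n = 24 (the maximum in section 10.3), 1/24 = 4.2 points. If only 12 paused (an assumption), 1/12 = 8.3 points.

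**The case against.** The best defence is that 3.5 is a cause-specific endpoint. It counts restarts for listed reasons, and requiring two values for rebound is a legitimate, stricter choice than a cautious clinical rule. Section 8.1.16 is also only a recommendation. On this view the two texts differ without contradicting each other, and 3.5 undercounts only if it was meant to cover every protocol-directed restart. That much stands: a confirmed-rebound count is worth reporting. It does not explain why the CD4 criterion, which plays the same part in both places, is 450 in one and 500 in the other, or why a protocol-directed restart should have no place in the restart endpoint.

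A reader might infer three stronger things, which the protocol does not support.

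- **That participants are put at risk by two CD4 cut-offs.** Section 8.1.16 is the rule sites act on and its cut-off of 500 is the more protective. Section 5.3.2 directs no clinical action.
- **That the affected pre-pause CD4 range can be stated.** The condition "CD4 cell count > 500 cells/ml at baseline" in section 7.3.1 governs the first vaccination at week 0. Sections 7.3.3 and 8.1.14 set no CD4 minimum for the pause, no reference count is named for the 50% drop, and the CD4 wording of 3.5 can be read two ways.
- **That every restart on a value below then above 2,000 is lost.** A day-7 value may rescue some. The flow chart and Attachments J, K and M are not reproduced, so further sampling cannot be ruled out.

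**Conclusion.** The point holds as a misalignment between an endpoint definition and the rule that produces its events. Read literally, 3.5 is a strict subset of the restart triggers in section 8.1.16, so any error is an undercount. That direction holds under both readings of the CD4 wording and does not depend on any event rate.

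The size cannot be derived. The protocol gives no frequency for the missed patterns, and the number may be zero. Each missed restart costs 4.2 points if all 24 pause, and more if fewer do.

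The consequence is minor. Item 3.5 is a descriptive secondary endpoint. A reader might suspect that the undercount flatters the efficacy result, but endpoint 3.4 and the >20% signal in section 10.1 rest on viral load staying below 2,000, not on restarts. The time-to-rebound analysis, as written there, does not refer to 3.5.

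**What to change.** In section 5.3.2, define 3.5 as the proportion in whom cART is restarted under any section 8.1.16 criterion, including a value below then above 2,000, laboratory abnormalities and clinical symptoms. Tabulate restarts by reason, with confirmed rebound (two values above 2,000) as one reported category so that the stricter count is kept. Print one CD4 cut-off in both sections. Keeping <500 leaves the operative safety rule unchanged. When rewording, state whether the 50% drop and the absolute cut-off are alternatives.

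The cost is wording in section 5.3.2, including the CD4 number, with no new visits or samples. The one downside is that the reported restart proportion may be slightly higher.

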## 7 SELECTION AND WITHDRAWAL OF SUBJECTS

### 7.1 INCLUSION CRITERIA

1. Subject included in ChAd-MVA.HIVconsv\_BCN01 study with complete follow-up and included in BCN01-RO extension study.
2. Willing and able to give written informed consent for participation in the study
3. Willing and able to keep a good adherence to their cART regimen for the duration of the intervention phase.
4. Optimal virological suppression for at least 3 years defined as maintained pVL below limit of detection (based on current available assays, 20 or 40 copies/ml) allowing for isolated blips (<200 cop/ml, non-consecutive, >10% total determinations).
5. Being on a non-boosted integrase-inhibitor based regimen (raltegravir or dolutegravir) for at least 4 weeks at screening visit.
6. No new AIDS-defining diagnosis or progression of HIV-related disease.
7. Haematological and biochemical laboratory parameters as follows:
  - a. Haemoglobin > 10g/dl
  - b. Platelets > 100.000/dl
  - c. ALT ≤ 2.5 x ULN
  - d. Creatinine ≤ 1.3 x ULN
8. Serology: negative for hepatitis B surface antigen; negative for hepatitis C antibodies OR confirmed clearance of HCV infection (spontaneous or following treatment).
9. Available for follow up for duration of study (baseline + at the most 54 weeks) and willing to comply with the protocol requirements
10. Age ≥18 years
11. CD4 T cell count ≥500 cells/mm^3

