### 10.1 RESPONSE EVALUATION (EFFICACY)

Two main efficacy endpoints will be evaluated in the BCN02-trial as follows:

Part A) Efficacy of the combined intervention (Kick & kill strategy) in the reduction of viral reservoir will be expressed by total HIV-1 DNA copies per million purified CD4+ T cells measured by quantitative digital droplet PCR (ddPCR) at baseline and 1 week after 3rd dose of RMD. Wilcoxon signed rank test will be used for comparisons.

Part B) Efficacy of HIVconsV vaccines in combination with RMD on viral rebound containment after treatment interruption will be evaluated by analysing the proportion of individuals who maintain sustained pVL <2,000 copies/ml at week 29 (12weeks after treatment cessation). Complementary, a survival analysis will be performed to describe time to rebound during the MAP period. Taking into consideration recent published data suggesting that early treatment initiation could favor a delayed viral rebound/spontaneous viral control in 10% in opposition to <5% in chronically-treated individuals, a positive efficacy signal has been established if at least >20% of individuals remain with pVL <2,000 copies/ml at w12 of MAP (pre-defined efficacy threshold).

Regarding virological and immunogenicity endpoints: Differences in the breadth and magnitude of different virological and immune parameters analyses between two longitudinal determinations in the same individuals will be assessed using a Wilcoxon signed-rank test. Correlations between the virologic, immune parameters and clinical outcome will be performed using Pearson test.

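### Endpoint 3.5 and section 8.1.16 fix different criteria for the same cART restart: CD4 below 450 versus below 500, and two pVL values above 2,000 versus the second value alone

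*Protocol*

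**What the plan says.** Endpoint 3.5 in section 5.3.2 is the proportion of participants in whom cART is restarted for listed reasons: "viral rebound (2 consecutive pVL >2,000 copies/ml 3-5 days apart), >50% drop in CD4 cell counts, <450" cells/mm3, and/or symptomatic acute retroviral syndrome.

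Section 8.1.16 gives the restart rules for the visit held 7-10 days after the first positive qualitative test. They use two quantitative viral loads, at pVL-pos and at pVL-pos+3d.

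- The first rule recommends immediate restart when both values exceed 2,000 copies/ml.
- The second recommends the same when only the later value does: "If viral load is <2,000 copies/mL in visits pVL-pos and >2,000 copies/mL in visit pVL-pos+3d".
- In both rules an and/or adds further triggers: "clinical symptoms, laboratory abnormalities or significant drops in CD4 T cell counts (>50% &/or <500) have been detected".
- The third rule leaves cART off when the second value is below 2,000 and none of those further triggers is present.

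Restart can also be decided outside this pathway. Section 8.1.15 has it discussed at every routine MAP visit, in the light of the clinical visit, "willingness of patients to resume treatment and detection of viral load in the qualitative test". Where blood results are due, CD4 falls are considered as well.

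**The concern.** Endpoint 3.5 counts restarts by reason, and section 8.1.16 supplies reasons for restarting. The two lists should agree, or the protocol should say why they do not. They disagree on two fixed values: the CD4 limit, and whether one or two viral loads above 2,000 copies/ml are needed.

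A site that follows 8.1.16 will restart some participants who, on the literal wording of 3.5, meet none of its criteria. The reported proportion could then understate protocol-recommended restarts. Two analysts could also reach different counts from the same data, depending on which section they treat as governing. In a trial of at most 24 people, one or two such cases would visibly move the figure.

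**Working it through.** There is no sample size, power or error-rate figure to reproduce. The check sets the two rules side by side and then works out what one omitted participant is worth.

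**Inputs**

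- Endpoint 3.5 (section 5.3.2): two consecutive values above 2,000 copies/ml, 3-5 days apart; CD4 fall above 50%; CD4 below 450; symptomatic acute retroviral syndrome.
- Section 8.1.16: pVL-pos+3d above 2,000, whatever the first value; CD4 fall above 50% and/or count below 500; clinical symptoms; laboratory abnormalities.
- Maximum enrolment (section 10.3): 24.

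The CD4 fall and the 450 limit in 3.5 are read as separate triggers, which is the reading that counts most restarts.

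**Step 1: compare the rules, taking each pattern as the only trigger**

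| Pattern | 8.1.16 recommendation | Meets 3.5 as written? |
|---|---|---|
| Both pVL above 2,000 | Restart | Yes |
| First below, second above 2,000 | Restart | Not on these two values |
| First above, second below 2,000 | No restart | No |
| CD4 fall above 50% | Restart | Yes |
| CD4 below 450 | Restart | Yes |
| CD4 450-499, fall of 50% or less | Restart | No |

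The rules diverge in two rows. In the second row the draws are three days apart, so the spacing in 3.5 is met, but only one value exceeds 2,000. In the last row the count is below 500 but not below 450. If the two CD4 items in 3.5 were read jointly, the CD4 gap would widen: a count below 450 without a halving would not qualify either.

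**Step 2: what one omission is worth**

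With n participants in the denominator, each omitted restart lowers the proportion by 1/n.

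- If all 24 enter the MAP: 1/24 = 0.0417, or 4.2 percentage points.
- Section 5.3.2 foresees that some may not enter after the futility analysis. With 12 entrants, a number assumed here for illustration only: 1/12 = 0.0833, or 8.3 points.

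Since n cannot exceed 24, 4.2 points is the smallest effect of one omission.

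**Step 3: how many omissions**

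This cannot be derived. It needs the CD4 distribution during the MAP and the frequency of a low first value followed by a high second one. The protocol gives neither, and the number may be zero.

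**The case against.** The strongest defence is that 3.5 is meant to be stricter than the clinical rule. Section 8.1.16 is a recommendation that protects the participant; 3.5 is an outcome definition. Requiring two consecutive values above 2,000 also matches the virological-failure definition in sections 7.3.1 and 7.3.2. This could justify the virological difference, although the protocol does not say so. It cannot explain 450 against 500, because 3.5 already includes CD4 and clinical reasons and no restart rule shown uses 450. Attachment M might show which limit is meant, but it is not available. Even if it agreed with one section, the other would still need correcting.

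A reader might infer more than the text supports, in four ways.

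- **Laboratory abnormalities as a third contradiction.** Section 8.1.16 names them and 3.5 does not. But section 8.1.15 lists transaminase elevation, lymphopenia and thrombocytopenia among the signs of acute retroviral syndrome, which 3.5 counts. The overlap is large enough that this is not a separate conflict.
- **Endpoint 3.5 as a pure subset of 8.1.16 restarts.** Someone with a negative qualitative test who restarts at a routine visit for symptoms or CD4 below 450 counts under 3.5 without ever reaching the 8.1.16 visit.
- **A calculable share of screens at which a third viral load completes the pair.** The routine quantitative draws are fixed: "Visits at 2, 4, 8, and 12 weeks after treatment interruptions (weeks 19, 21, 25 and 29) will also include". But external laboratory results take 72 hours, visits have a window of plus or minus 2 days, and the resumption visit spans days 7-10. The protocol also does not state that routine draws continue alongside the positive-test pathway. A sample taken on the day of restart would not normally be its reason.
- **A small CD4 fall is enough to reach the gap.** Entry requires "CD4 T cell count ≥500", so this holds for someone sitting at exactly that floor. No CD4 distribution is given, and the entry count is not the count when the pause starts.

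**Conclusion.** The inconsistency is real and lies in the current text. The same restart decision carries CD4 limits of 450 and 500 cells/mm3, and a two-value and a second-value virological trigger. Nothing shown reconciles them. Each affected participant lowers the 3.5 proportion by at least 4.2 points, on the assumption that the denominator is those who enter the MAP, at most 24. A case is lost only if the divergent criterion was the sole reason for restart.

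The point is minor. Endpoint 3.5 is a descriptive secondary endpoint with no threshold, test or stopping role. A reader might infer that the trial's efficacy signal is compromised, but that signal is defined separately in section 10.1: "a positive efficacy signal has been established if at least >20% of individuals remain with pVL <2,000 copies/ml at w12 of MAP". The documents likewise support no claim of a safety defect or of an error in the time-to-rebound analysis.

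**What to change.** 1. Choose one CD4 limit and one virological trigger, and use them in sections 5.3.2 and 8.1.16 and in Attachment M. Since participants are managed by 8.1.16, the simplest choice is to carry its values (count below 500; second value above 2,000 copies/ml) into 3.5. If 450 is the limit intended on clinical grounds, change 8.1.16 instead.
2. Define 3.5 as the proportion of participants whose cART is restarted on those criteria at any MAP visit, whether a routine visit under 8.1.15 or a visit in the positive-test pathway. Tying it to the 8.1.16 visit alone would leave restarts decided at routine visits unclear.
3. If a confirmed-rebound count based on two values above 2,000 is also wanted, say so and report it as a separate line.

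The cost is amendment wording only, with no extra visits or samples.
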